#### Culture

Sputum is transferred with a cotton swab to an agar plate with 5% sheep blood (Beckton Dickinson) with a *Staphylococcus aureus* streak and a Chrom Orientation agar plate (Beckton Dickinson), and the inoculum is streaked over the agar surface. The blood agar is incubated at 35 °C in an atmosphere with 6% CO_2_, and the Chrom-agar orientation is incubated at 35 °C in normal atmospheric conditions.

After 1–2 days of incubation, pathogens are identified and tested for antimicrobial susceptibility.

The pathogen identified by culture will be semi-quantitatively assessed as numerous, some, or few, with a morphology description. Mixed flora judged to be pharyngeal flora will be registered as “pharyngeal flora”. No growth of pathogens will be registered as “No growth of pathogens”.

### Baseline variables {25}

Demographics, symptoms, and smoking are collected from a patient interview. Vital parameters, comorbidities, suspicion of pneumonia, diagnostic packages [33], severe acute respiratory syndrome coronavirus 2 (SARS-CoV-2), disease severity assessment (CURB-65 [34], PSI [35], and Danish Emergency Process Triage (DEPT) [36]), blood tests (C-reactive protein, leucocytes, neutrophils) length of hospital stay, antibiotic consumption, and inhaled medicine are extracted from the patient’s medical record (Table 1).

**Table 1 Tab1:** Demographic and baseline clinical characteristics

Variable	Overall	Group 1 total (*n* =)	Group 2 total (*n* =)
		Tracheal suction (*n* =)	Forced expiratory technique (*n* =), induced sputum (n =)
Site			
Aabenraa			
Sønderborg			
Sex, *n* (%)			
Age, mean (SD)			
Smoking status			
Current smokers, *n* (%)			
Ex-smokers, *n* (%)			
Non-smokers, *n* (%)			
Symptoms			
Cough, *n* (%)			
Expectoration, *n* (%)			
Chest tightness, *n* (%)			
Dyspnea, *n* (%)			
Severity assessment			
CURB-65 score* 0–1, *n* (%)			
CURB-65 score* 2, *n* (%)			
CURB-65 score* 3–5, *n* (%)			
PSI* risk class 2–3, *n* (%)			
PSI* risk class 4, *n* (%)			
PSI* risk class 5, n (%)			
Triage level 1, *n* (%)			
Triage level 2–3, *n* (%)			
Triage level 4–5, *n* (%)			
Diagnostic packages			
Airways symptoms, *n* (%)			
Fever, *n* (%)			
Dyspnea, *n* (%)			
Unspecific illness, *n* (%)			
Suspicion of COVID-19 infection, *n* (%)			
Other, *n* (%)			
Suspicion of pneumonia, *n* (%)			
SARS-COV-2 positive at admission, *n* (%)			
Comorbidities			
COPD*, *n* (%)			
Asthma, *n* (%)			
DM*, *n* (%)			
CVD*, *n* (%)			
Cancer, *n* (%)			
Other, *n* (%)			
Vital parameters			
SaO_2_*, mean (SD)			
RR*, median (IQR)			
HR*, median (IQR)			
Systolic blood pressure, median (IQR)			
Diastolic blood pressure, median (IQR)			
Fever > 38 °C, *n* (%)			
Altered mental status, *n* (%)			
Blood tests			
C-reactive protein, mean (SD)			
Leucocytes, mean (SD)			
Neutrophils, mean (SD)			
Did the patient receive antibiotic treatment			
Within 1 month, *n* (%)			
Before sputum collection, *n* (%)			
Inhaled medications, *n* (%)			
Length of hospital stay, mean (SD)			

**CURB-65 score*, score for pneumonia severity based on confusion, urin, respiratory rate, blood pressure, and age; *PSI*, Pneumonia Severity Index; *COPD*, chronic obstructive pulmonary disease, *DM*, diabetes mellitus type 1 and type 2; *CVD*, cardiovascular disease; *SaO*_*2*_, oxygen saturation; *RR*, respiratory rate; *HR*, heart rate

### Co-variables

Co-variables (listed and defined below) will be measured and compared between the two allocation groups. Patients’ symptoms, oxygen saturation, respiratory rate, and overall experience will be measured before (right after allocation) and after sputum collection (measured at the latest 10 min after the procedure). Side effects observed by the project assistants and experience by the patient during the procedure will be registered once after sputum collection. Data on mortality and re-admission will be extracted from the patient medical record. The projects assistants will follow standardized protocols to register all the co-variables including the questions concerning patient experiences.
C*oughing, expectoration, dyspnea, and chest pain* symptoms will be reported as binary variables. Aggravation of cough, expectoration, dyspnea, and chest pain experienced by the patient will be reported.*Oxygen saturation.* Oxygen saturation (SaO_2_) will be measured using a pulse oximetry device to measure arterial oxygen saturation level in percentages up to 100%. The acceptable SaO_2_ is ≥ 93%. For patients with chronic obstructive disease, a SaO_2_ is acceptable at ≥ 88%. SaO_2_ will be reported as mean (standard deviation (SD)) [37].*Respiratory rate.* The respiratory rate (RR) will be counted by the professional attending the patient. The respiratory rate is the number of breaths per minute that a patient takes while resting. It is assessed by counting the number of times the patient’s chest rises in half a minute multiplied by two. RR will be reported as mean with standard deviation (SD). Acceptable results for RR are between 12 and 20 times per minute [38].*Side effects observed by the project assistants.* Project assistants will register any side effects such as bleeding from the airways and bronchospasm.*Short-term mortality.* Mortality within 7 days from admission to the emergency department*Re-admission.* Re-admission to hospital within 30 days of the original discharge*Patient’s overall experience of symptoms.* Patient wellbeing and overall experience of symptoms will be measured at the latest 10 min after sputum collection. Patients will asked to verbally score their overall experience of their symptoms based on the CR10 Borg scale [39, 40]. The CR10 Borg scale assess the experience of patient symptoms ranges from “0= nothing at all” to “10 very very strong” and over 10 as “maximal” [40]. A visual support tool describing this scoring system will be used to assist the patient and the ordinal result will be reported as mean and SD.*Patient’s experience of the procedure to collect sputum sample*: This will be measured once after an attempt at sputum collection. Patients will be asked to give a verbal score to the question: “What was your experience of this procedure?” using a five-point Likert scale. This scale ranges from “very bad, bad, neither bad nor good, good, very good”. A visual support tool describing this scoring system will be used to assist the patient. The result will be reported in percentages. The development and validation of this scale was based on individual and focus group interviews using cognitive interview methods [41].

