### Randomization {10}

Within an hour after recruitment, enrolled patients are randomly assigned to either control (sputum collection by tracheal suction) or intervention (sputum collection by forced expiratory techniques). Patients in the intervention group who cannot deliver a specimen will undergo tracheal suction according to regional guidelines, and these samples will not be included in the primary analyses.

Patients are allocated 1:1 according to a computer-generated randomization sequence without stratification using blocks of six programmed by an independent data manager, so the treatment assignment is made by chance and the allocation is completely independent of any prior treatment allocation to a patient. The randomization tool in Research Electronic Data Capture (REDCap) will be used [29, 30]. The project assistants administering the randomization will not have access to the randomization code and will be blinded to the randomization procedure, block sizes, and randomization sequence at all times during the trial period. In addition, allocation concealment is ensured, as the randomization is performed electronically, is not revealed before consent is obtained, and occurs immediately prior to sputum collection.

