#### Blinding

Participants, project assistants, and outcome adjudicators are not blinded to the randomization as it is not possible. The investigator will be blinded until data analysis is completed.

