### Exposure variables

#### Tracheal suction

Before tracheal suction is performed, the patient will be informed in detail about the procedure. The patient is introduced to Fowler’s position (semi-sitting position in 45–60° with knees either bent or straight) and encouraged to clear their airway with a deep cough. The catheter (EXTRUDAN Surgery Aps, Denmark, CH12, 530 mm) tip is lubricated with Xylocaine (lidocaine HCl) 2% jelly and inserted into the nares during inhalation and gently advanced about 40 cm without applying suction. The suction catheter port is covered, and suctioning is performed before withdrawing the catheter. Suction is set at 200–400 mmHg negative pressure. If necessary, the specimen is diluted in sterile saline water before storage in a sterile container.

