### Harms {30}

The project includes collecting methods that are already applied and recommended in clinical practice. There are minimal indications of adverse effects of a spontaneous cough or induced sputum after inhaling an isotonic saline solution (0.9%) [21, 22]. It is known that the tracheal suction routine carries a risk of airway bleeding, although this is rare and often short-lived [20]. Moreover, there may be short-term discomfort, especially during the tracheal suction procedure [19]. Patients will be informed of the adverse events verbally and in writing. In case of an aggravation of symptoms, the procedure that is being performed will be interrupted preventing patient participation. The procedures are known to have minimal risks and the hospital will provide routine ancillary post-trial care, if necessary.

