#### Definition of analyses population {20}

The primary analysis will be conducted according to the intention-to-treat (ITT) principle [46, 47].

We define the ITT population as all admitted patients suspected of LRTI who sign informed consent and subsequently are allocate to one of two sputum collection groups. Sputum samples obtained by tracheal suction from patients in the intervention group, who are not able to expectorate, will be analyzed separately from the ITT analyses.

The primary analysis compares the tracheal suction group and the expiratory technique group to identify the most effective method for obtaining good quality sputum samples. The secondary analysis consists of an agreement analysis [48] between forced expiratory technique alone and forced expiratory technique after sputum induction.

Additionally, analysis of the secondary outcome of adverse effects will be conducted at baseline (right after allocation) and at the latest, 10 min. after the intervention. Clinical symptoms (cough, expectoration, chest pain, or dyspnea), SaO_2_, RR, and CR10 Borg scale [40] will be measured. Furthermore, a 5-point Likert scale will be used to measure patient experience of the procedure. The analyses will be adjusted for variables with a large influence on the outcome, which is an odds ratio larger than 2, to accommodate bias [49].

Descriptive analyses will be performed on the pathogens found when the specimens are cultured according to differential quality criteria.

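### The reference readings that define worsening in secondary outcome 1 are taken after allocation is known, so the baseline can itself differ by arm; the size and direction of the resulting bias are not known

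*SAP article*

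**What the plan says.** The Co-variables section fixes the timing: symptoms, SaO2, RR and overall experience "will be measured before (right after allocation) and after sputum collection", the second reading being no later than 10 minutes after the procedure. Definition of analyses population {20} repeats it and calls that moment baseline: "analysis of the secondary outcome of adverse effects will be conducted at baseline (right after allocation".

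Randomization {10} says that allocation "is not revealed before consent is obtained, and occurs immediately prior to sputum collection". Under Blinding: "Participants, project assistants, and outcome adjudicators are not blinded to the randomization as it is not possible". On measurement: "The respiratory rate (RR) will be counted by the professional attending the patient", and "The projects assistants will follow standardized protocols to register all the co-variables". No blinded assessor is named for these readings.

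Outcome definitions {26} builds secondary outcome 1 from seven binary items. Four refer to worsening or occurrence: SaO2, RR, symptoms, and the patient's experience of symptoms (CR10 Borg). The other three are side effects seen by the assistant, death within 7 days and re-admission within 30 days. The number of events goes into a mixed effect Poisson model.

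**The concern.** A reference value for change should not depend on the treatment assigned. Here it is read when one group has just been assigned a suction catheter and the other breathing and coughing exercises. The plan itself gives a reason to expect different reactions: "Before tracheal suction is performed, the patient will be informed in detail about the procedure", and Harms {30} says "there may be short-term discomfort, especially during the tracheal suction procedure". RR, dyspnea and the Borg score can respond to anticipation, and an unblinded assistant registers them.

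If the suction group's baseline is raised for these items, a later value is less likely to count as worse. That would shrink, or even reverse, the adverse-event contrast between arms, which is the trial's second objective. Standardized registration, the only safeguard stated, changes neither the timing nor the knowledge of allocation.

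**Working it through.** **Textual check.**
1. The post-allocation baseline is given in two separate sections, so it is not a slip in one place.
2. Allocation follows consent, comes immediately before collection and is open to patient and assistant. No step withholds it until the baseline has been read.
3. No pre-allocation value is named as the reference for worsening. Baseline variables {25} takes vital parameters from the medical record without stating when they were recorded.

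**Numerical illustration for the RR item.** The plan gives no figure to reproduce, and every input below is an assumption.
- True RR: mean 22, SD 5. Measurement error: SD 2 at each reading. Counts rounded to even numbers (half a minute times two).
- Both procedures truly raise RR by 2.
- Pre = true + s + error, where s is the anticipatory rise in the suction arm.
- Post = true + 2 + p·s + error, where p is the share of the rise still present at the second reading.
- Event: post > pre and post > 20. Adding the below-12 limb changes the results by less than half a point.

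Suction-arm event rate:

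| Share persisting (p) | s = 0 | s = 1 | s = 2 | s = 3 |
|---|---|---|---|---|
| none | 48.9% | 39.4% | 29.4% | 20.3% |
| half | 48.9% | 45.8% | 42.0% | 37.5% |
| all | 48.9% | 52.4% | 55.2% | 57.5% |

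Difference from s = 0, which is also the rate in the expiratory arm under these inputs:
- None persisting: 48.9 − 39.4 = 9.5 points, up to 48.9 − 20.3 = 28.6 points lower.
- Half persisting: 48.9 − 45.8 = 3.1, up to 48.9 − 37.5 = 11.4 points lower.
- All persisting: 52.4 − 48.9 = 3.5, up to 57.5 − 48.9 = 8.6 points higher, because more patients exceed 20.

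With no true rise and none persisting, the rates are 25.0%, 17.4%, 11.1% and 6.4%, so suction looks 8 to 19 points safer. With mean RR 16 and a true rise of 2, the full-decay gap is about 4 to 12 points.

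**Borg item** (assumed mean 4, SD 2, error SD 0.7, true suction effect +1, post > pre, full decay): 68% with no shift, then 59%, 50% and 31% for shifts of 0.25, 0.5 and 1, against 31% in the expiratory arm. A shift equal to the true effect all but removes the contrast.

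**SaO2 item** (assumed mean 95, SD 2.5, error SD 1, true suction effect −1; post < pre and at or below 93): 31% with no shift, 39% with a baseline 1 point higher, 20% with one 1 point lower. Masking here needs a lowered baseline.

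**The case against.** The strongest objection concerns direction. Masking needs the anticipatory rise to fade by the second reading, at most 10 minutes after the procedure. If it persists in full, suction looks worse, not better, as the table shows. Unblinded post-procedure readings could also push either way. This stands: a reader might infer that the design lowers the suction arm's event count, but the document supports only that it can.

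Several narrower objections also stand.
- A raised SaO2 baseline creates events, and pulse oximetry is the reading least likely to shift.
- Cough and expectoration are not plausibly raised by anticipation. The symptom item may also rest partly on worsening reported directly by the patient, with no subtraction from baseline.
- The moment at which the patient learns the arm is inferred from the timing and the lack of blinding; it is not stated.
- Patients are told of adverse events verbally and in writing. If that happens at consent, a pre-allocation reading carries some anticipation too, though it would then be common to both arms.
- It is tempting to say that no analysis can repair this. That is too strong: post-procedure RR and SaO2 by arm are a randomized comparison that needs no baseline.

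The plan's timetable has recruitment ending in July 2021, so a change of timing may reach few patients or none. That limits the remedy for data already collected but does not make a post-allocation baseline sound.

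**Conclusion.** The point holds as a weakness in how part of one secondary outcome is measured. The timing, the lack of blinding and the dependence of four items on that reading are all in the text. The most plausible consequence is masking of worsening in the suction arm for RR, dyspnea and Borg score, with SaO2 the least plausible.

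The size and sign cannot be established from the document. For RR, at a mean of 22, a true rise of 2 and shifts of 1 to 3 breaths per minute, the suction event rate moves from about 29 points too low to about 9 points too high, depending on how much anticipation persists. Only single items were modelled, so no effect on the Poisson count is claimed. Observed side effects, death, re-admission and the primary outcome do not use this baseline. The change is worth making, but the point does not threaten the trial's main conclusion.

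**What to change.** In Co-variables and in Definition of analyses population {20}, state that symptoms, SaO2, RR and CR10 Borg score are recorded after consent and before the REDCap allocation is opened. In Outcome definitions {26}, define every worsening item against that value. Consent already precedes allocation, and up to an hour may pass between recruitment and allocation, so the same staff can take the same readings slightly earlier.

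For patients already measured after allocation, do not relabel the data. Instead:
- state the limitation in the plan and the report;
- add a sensitivity analysis comparing post-procedure RR, SaO2 and Borg score directly by arm;
- state that a null or suction-favouring result on the worsening items will not be read as evidence of safety.

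The cost is a change of wording and of the order of data entry. If the change is made during recruitment, there will be two baseline definitions, so record for each patient which one applied. The sensitivity analysis needs no new data. It removes dependence on the baseline but not the lack of blinding at the second reading.

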## Background {7}

Lower respiratory tract infection (LRTI) is a serious condition associated with high mortality, morbidity and economic burden [3–5]. Appropriate and targeted antimicrobial treatment is vital to avoid unnecessary use of broad-spectrum antibiotics and subsequent development of bacterial resistance.

Sputum Gram stain and culture from patients with LRTI are important when selecting a targeted antimicrobial treatment [6, 7].

Several clinical limitations interfere with the practice of obtaining a representative specimen from the lower respiratory tract (LRT). Many patients find it difficult to expectorate, sputum is often contaminated by oropharyngeal microbiota, and some patients have already been treated with antibiotics at admission, compromising the results from sputum culture [8–10]. The guidelines from the American Thoracic Society and Infectious Diseases Society of America recognize the challenges in obtaining a valid sputum sample. They recommend sputum analyses based on individual clinical assessment, local etiological considerations, and local antimicrobial stewardship [11].

The Danish guidelines [12] follow the National Institute for Health and Care Excellence guidelines [13] and are further developed by experts in the fields of microbiology, infectious disease, and emergency medicine. It is required that sputum samples must be collected at arrival at the emergency department (ED) from all patients admitted with suspected LRTI, and advocate tracheal suction as an optimal collecting method [12]. Despite indications from some studies that tracheal suction might be superior to expectorated sputa in diagnosing LRTI [14, 15], low accuracy and misclassification of poor samples have been reported [16, 17]. Tracheal suction is widely performed to clear pulmonary secretions in mechanically ventilated patients [18] but reported as a painful experience for the patient [19] being associated with adverse events such as hypoxia, oxygen desaturation, and mucosal bleeding [20]. Forced expiratory technique and sputum induction are considered safe and straightforward methods [21] and are used successfully to clear airways and increase sputum production, facilitating collection for microbiological analyses when patients are unable to expectorate [22–25].

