#### Sputum samples collected by forced expiratory techniques

These techniques are based on the patients’ own attempts to deliver a sputum sample. The patient is brought into a 90° sitting position and instructed to clear the mouth with water to minimize oropharyngeal contamination, and proper forced exhalation and the coughing technique are thoroughly explained [24, 31].

The patient takes 3 to 5 deep diaphragmatic breaths, inhaling through the nose, exhaling through pursed lips. The patient takes a normal breath and then squeezes it out by contracting the abdominal and chest wall muscles, with the mouth and glottis open, while whispering and forcing the word “huff” during exhalation. The procedure is repeated 3 to 5 times. As secretions enter the larger airways, the patient exhales from high-to-mid lung volume to clear secretions from more proximal airways. The procedure continues as the patient takes 3 to 5 relaxed diaphragmatic breaths before coughing again [24, 31]. The sputum sample is stored in a sterile container.

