#### Induced sputum

Isotonic saline inhalation (0, 9%) is used to loosen and induce the sputum. It is given for 10 min with a nebulizer system (Unomedical Opti-Mist TM,2.1m, ref. 93-772mm) [22]. After that, a forced expiratory technique is performed, and the sputum sample is stored in a sterile container.

Inhalation medicine is permitted as part of concomitant care.

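### Secondary outcome 1 counts cough and expectoration as adverse events, although they are the means and the goal of the expiratory techniques, and no rule separates intended effect from harm

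*SAP article*

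**What the plan says.** Outcome definitions {26} defines secondary outcome 1 as a number of adverse events. One of its seven components is a binary item, met when cough, expectoration, dyspnea or chest pain newly occurs or gets worse. The Co-variables section supplies the measurement: "Aggravation of cough, expectoration, dyspnea, and chest pain experienced by the patient will be reported". Symptoms are read right after allocation and again no later than 10 minutes after the procedure.

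Analysis for secondary outcomes compares the total between arms in a mixed effect Poisson model. It adds a chi-square or Fisher test per event type in Table 5, where cough and expectoration each have a row. No total without these two symptoms is planned.

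On the expiratory arm, the SAP says:

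- Background {7}: the techniques "are used successfully to clear airways and increase sputum production".
- Forced expiratory techniques: "These techniques are based on the patients’ own attempts to deliver a sputum sample", and "The procedure continues as the patient takes 3 to 5 relaxed diaphragmatic breaths before coughing again".
- Induced sputum: saline "is used to loosen and induce the sputum". "After that, a forced expiratory technique is performed, and the sputum sample is stored in a sterile container".

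On the suction arm, the catheter draws the specimen, but the patient is first "encouraged to clear their airway with a deep cough".

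**The concern.** Objective 2 asks whether the number of adverse events differs between the methods, and the Poisson comparison of secondary outcome 1 is the analysis meant to answer it. If the count includes what one arm's procedure is designed to produce, it partly measures allocation and success rather than harm. An enrolled patient who was not expectorating at baseline and then delivers a sample can meet the definition of a new symptom, while providing the specimen that the primary outcome needs. A successful suction sample requires no expectoration.

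Two errors could follow. The expiratory techniques could look more harmful when they are not, or a real excess of harm from suction could be cancelled.

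There is also a loss of information. If the four symptoms form one binary item, as Outcome definitions {26} reads, expectoration alone can fill it. New dyspnea or chest pain in the same patient then adds nothing to the count.

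**Working it through.** **Step 1: what can be reproduced.** The SAP states no event rate, rate ratio or power for secondary outcome 1, so there is no figure to reproduce. Everything numerical below is an illustration under assumed rates.

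**Step 2: direction, symptom by symptom.**

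- *Expectoration.* In the expiratory arm it is the goal; in the suction arm it is not needed. Eligibility {22} requires only one of dyspnea, cough, expectoration, chest pain or fever, so patients without baseline expectoration are enrolled and can score a new occurrence. The direction is against the expiratory arm.
- *Cough.* It is part of the expiratory procedure, but suction patients are also asked for a deep cough before a catheter is passed. The direction is uncertain.

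**Step 3: inputs for the illustration.**

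- From the SAP: 260 patients allocated 1:1, so 130 per arm; significance level 0.05, taken as two-sided.
- Assumed, other six items, both arms: 0.10 + 0.15 + 0.20 + 0.10 + 0.03 + 0.15 = 0.73 events per patient.
- Assumed, symptom item: 0.30 under suction and 0.30 + x in the expiratory arm, where x is the excess due to intended cough or expectoration.
- Assumed, masking case (suction truly worse): SaO2 item 0.25 v 0.10, side effects 0.25 v 0.10, Borg item 0.30 v 0.20. The other suction items then sum to 0.25 + 0.15 + 0.30 + 0.25 + 0.03 + 0.15 = 1.13.

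Items are simulated as independent, without random effects. The test is z = ln(E/T) / √(1/E + 1/T), where E and T are the total events in the expiratory and suction arms, with a cut-off of 1.96.

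**Step 4: results.**

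No true harm difference: rate ratio = (0.73 + 0.30 + x) / (0.73 + 0.30) = (1.03 + x) / 1.03. Masking case: rate ratio = (1.03 + x) / (1.13 + 0.30) = (1.03 + x) / 1.43.

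| Excess x | Rate ratio, no true difference | Falsely finds expiratory worse | Rate ratio, suction truly worse | Power to show suction worse |
|---|---|---|---|---|
| 0 | 1.00 | 1.4% | 0.72 | 86% |
| 0.05 | 1.05 | 4% | 0.76 | 74% |
| 0.10 | 1.10 | 9% | 0.79 | 58% |
| 0.20 | 1.19 | 30% | 0.86 | 25% |
| 0.30 | 1.29 | 62% | 0.93 | 6% |
| 0.40 | 1.39 | 88% | 1.00 | 1% |

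Percentages are simulated and accurate to about one point. The reference of 86% uses a symptom item of 30% in both arms, so that only the excess changes down the column.

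**Step 5: the reverse case.** Suppose suction provokes more cough, with the item at 0.50 under suction and 0.30 in the expiratory arm. With 0.3, 0.6 or 1.0 other events per patient, the ratio is 0.60/0.80 = 0.75, 0.90/1.10 = 0.82 or 1.30/1.50 = 0.87. The distortion then favours the expiratory arm, and the net sign depends on which symptom dominates.

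**The case against.** The strongest reply is that the item is not a tally of coughs or of sputum produced. It is a patient-reported reading, taken within 10 minutes after the procedure under standardized protocols that are not shown. Patients who already cough or expectorate can score only by getting worse. This stands: a delivered sample may score an event but need not. A reader might infer that every successful expiratory sample is counted as a harm; the text does not support that.

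A reader might also infer that the harm comparison as a whole is biased against the expiratory arm. That is established only for expectoration. With cough asked for in both arms, and possibly provoked by the catheter, the net direction is not proven.

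Table 5 gives cough, expectoration, dyspnea and chest tightness separate rows and tests, so new dyspnea is not hidden from a reader of that table. This stands too, but the table does not correct the Poisson total. A single binary item would also cap the symptom contribution at one event per patient, which limits the distortion without removing it.

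Finally, the rates are assumed, and excesses of 5 or 10 points do much less damage than 20 to 40. That is why the full range is shown. None of these replies supplies a rule that separates the intended effect from harm.

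**Conclusion.** The point holds in a limited form. Secondary outcome 1 counts as adverse two symptoms that one arm's procedure is designed to produce, with no rule to distinguish the two. The distortion runs against the expiratory arm for expectoration and is of uncertain direction for cough.

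Its size cannot be computed from the SAP. Under the assumed rates, the chance of wrongly finding the expiratory arm worse rises from 1.4% to about 9% at a 10-point excess and about 30% at 20 points. If suction is truly worse as assumed, power falls from about 86% to about 58% and 25% at the same excesses. These figures rest on independent items, no random effects and the item rates listed above.

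The severity is should-fix. A secondary outcome is affected; the primary comparison of sample quality is not.

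**What to change.** Before database closure:

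1. In Outcome definitions {26}, build the symptom item of the main adverse-event count from dyspnea and chest pain only.
2. Keep cough and expectoration in Table 5 by arm, labelled as expected procedure effects rather than adverse events.
3. Keep the count as now defined, with cough and expectoration included, as a prespecified sensitivity analysis under the same Poisson model, so that cough provoked by suction is not lost.

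The cost is wording and one further model run. No new data are needed, because the symptoms are already recorded separately. The downside is that distressing cough leaves the main count. It remains in the sensitivity count and can still register through the Borg item and the five-point experience scale. Making the change before the data are seen avoids the appearance of a data-driven choice.
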